## Abstract

**Background:**

Congenital brain lesions expose infants to be at high-risk for being affected by neurodevelopmental disorders such as cerebral palsy (CP). Early interventions programs can significantly impact and improve their neurodevelopment. Recently, in the framework of the European CareToy (CT) Project (www.caretoy.eu), a new medical device has been created to deliver an early, intensive, customized, intervention program, carried out at home by parents but remotely managed by expert and trained clinicians. Reviewing results of previous studies on preterm infants without congenital brain lesion, the CT platform has been revised and a new system created (CT-R).

This study describes the protocol of a randomised controlled trial (RCT) aimed to evaluate, in a sample of infants at high-risk for CP, the efficacy of CT-R intervention compared to the Infant Massage (IM) intervention.

**Methods/design:**

This RCT will be multi-centre, paired and evaluator-blinded. Eligible subjects will be preterm or full-term infants with brain lesions, in first year of age with predefined specific gross motor abilities. Recruited infants will be randomized into CT-R and IM groups at baseline (T0). Based on allocation, infants will perform an 8-week programme of personalized CareToy activities or Infant Massage. The primary outcome measure will be the Infant Motor Profile. On the basis of power calculation, it will require a sample size of 42 infants. Moreover, Peabody Developmental Motor Scales-Second Edition, Teller Acuity Cards, standardized video-recordings of parent-infant interaction and wearable sensors (Actigraphs) will be included as secondary outcome measures. Finally, parents will fill out questionnaires (Bayley Social-Emotional, Parents Stress Index). All outcome measures will be carried out at the beginning (T0) and at end of 8-weeks intervention period, primary endpoint (T1). Primary outcome and some secondary outcomes will be carried out also after 2 months from T1 and at 18 months of age (T2 and T3, respectively). The Bayley Cognitive subscale will be used as additional assessment at T3.

**Discussion:**

This study protocol paper is the first study aimed to test CT-R system in infants at high-risk for CP. This paper will present the scientific background and trial methodology.

**Trial registration:**

NCT03211533 and NCT03234959 (www.clinicaltrials.gov).

## Background

Cerebral Palsy (CP), a clinical outcome linked to pre- or perinatal brain injury, represents the main chronic condition of disability in childhood [1, 2]. Disorders and disabilities associated with CP determine a relevant social, financial and emotional influence, on CP subjects, on their relatives, and also on health services, since these patients require continuous care, treatment and social support throughout their entire lives [3, 4]. The combined use of assessment tools such as the General Movement Assessment (GMA) according to Prechtl (GMs) and brain Magnetic Resonance Imaging (MRI) have shown high sensitivity and specificity in CP identification in infants since their first months of life [5]. In particular, a recent literature review has shown that brain MRI associated with GMA or neurological examination (Hammersmith Infant Neonatal Examination, HINE) performed at around full-term age determines the greatest predictive power of CP in high-risk newborns [6]. Early diagnosis has considerable importance because it allows for an early medical response and intervention which, as indicated by literature, can improve developmental outcome of high-risk children [7]. Moreover, early intervention (EI) is crucial because it targets brain plasticity, which for many functions has a maximum expressivity in an early limited time window or “critical period” [8, 9].

Several EI programs, based on Environmental Enrichment (EE) and Goal Directed approaches, have been used in clinical settings with positive results on neurodevelopment, but these findings are not conclusive due to high heterogeneity of clinical studies and applied intervention models [10–13].

In general, EIs should include certain essential characteristics to be effective and more specifically they should be early, intensive, personalized, multi-axial, family-centred and affordable for families and health services. In this context, biotechnologies and tele-rehabilitation appear to be promising approaches that can help achieve these standards [14].

Recently, in a European project (www.caretoy.eu, Trial Registration: NCT01990183), the CareToy (CT) system has been created. It is a technological and modular system able to provide, by means of tele-rehabilitation, a home and personalized intervention for very young infants (for further details see [15, 16]). CT allows subjects to carry out an early, intensive, individual EI carried out at home by parents consisting of highly customized exercises (rehabilitative packages called scenarios) remotely monitored by a clinical staff [15–18].

CT has been recently validated as a EI tool through a RCT study (CareToy training vs Standard Care), preceded by a pilot study, which involved a total of 61 in preterm infants born from 28 to 32 weeks of gestational age, without brain lesions and therefore considered at low risk for neurodevelopmental disorders. Children recruited in the pilot and RCT studies were divided into CT and Standard Care groups. Children allocated to the CareToy group followed a 4 weeks training with CT system, at the same time children allocated to the control group performed only Standard Care. All children were assessed with specific and standardized scales and questionnaires, immediately before and immediately after treatment period. Results of the study showed that CareToy training has a positive effect on promoting short-term visual and motor infant’s development [19, 20].

Based on these findings, the purpose of this study is to compare, through a Randomized Controlled Trial (RCT), the effects of two types of EI (CareToy training vs Infant Massage) on neurodevelopment of a group of at least 42 children at high risk for CP. The general hypothesis is that the CareToy system, with some adaptations, could be a useful EI tool also in brain-lesioned children at high risk for CP, effectively promoting motor, cognitive and perceptual development. In order to provide an EI to all children participating in the study, it was decided to offer Infant Massage (IM) as a valid alternative to CareToy. The choice of proposing IM was favoured by its ever-increasing application in Neonatal Intensive Care Units (NICU) [21]. The general hypothesis of IM intervention is that tactile stimulation (parent-infant) is able to promote neurodevelopment, emotional regulation of behavioural states and parent-infant relationship [22]. The rationale underlining these mechanisms seems attributable to increased metabolic efficiency and reduction of stress hormone synthesis. A recent systematic review [22] highlighted the effectiveness of IM on promoting neurodevelopment of preterm babies [23]; moreover, although studies on IM in infants with early brain damage are still limited, it seems to have positive effects on muscle tone and general motor development [24].

Based on this state of the art, the main purpose of this study is to evaluate the effects of CareToy EI (with a revised version of CareToy designed for this purpose), compared to those of Infant Massage, on neurodevelopment of infants at high risk for CP.

## Methods/design

This paper presents the protocol of an RCT which compares the effects of CareToy training to those of Infant Massage on neurodevelopment of infants at high risk for CP. Details of the two treatment protocols are described below.

### Ethical considerations

Tuscan Region Paediatric Ethics Committee (Italy) approved this study (no. 84/2017). Before the signing of informed consent, a dedicated personnel will verbally inform all parents of eligible infants about the trial, giving them also written informative material. Two informed consent forms during two different phases of the study will be provided. The first form allows for an observational phase related to a standardized GMA from the writhing period up to the fidgety one. Then, a second consensus form related to the intervention phase (CareToy or IM) will be given only to parents of infants with fidgety absent. There is a dual purpose for offering two treatments: to compare the two EIs and, for ethical reasons, to allow all eligible infants to carry out an EI.

### Primary objective

The main aim of the present trial is to explore the effects of CT training on neurodevelopment of infants at high risk of CP and then compare these effects to those of IM.

Three hypotheses have been specified:CareToy Revised (CT-R) is a useful rehabilitative medical device for young infants (< 1 year) at high risk for CPInfants receiving CT-R training will develop motor, perceptual and cognitive abilities faster than infants receiving IMImprovement in visual and motor abilities will be faster during CT-R training than during IM.

The secondary aim is to investigate the different impact of CT-R on neuromotor development, both quantitatively (postural, motor and manipulation competences) and qualitatively (motor repertoire and adaptive abilities). Moreover, another purpose is to measure the efficacy of CT-R training on visual and cognitive development, parent-infant interaction and sleep-waking pattern.

The two phases of this project will be preceded by a small pilot study in which feasibility of EI effects of CareToy Revised system (CT-R training) compared with Infant Massage (IM) will be evaluated.

### Study design

To make a comparison between the effects of CT training and IM in brain-damaged infants, a multicentre, evaluator-blinded, paired RCT will be carried out.

The involved clinical centres are the Department of Developmental Neuroscience, IRCCS Fondazione Stella Maris in Pisa; the Neonatal Intensive Care Unit of University Hospital “Santa Chiara” in Pisa, the Neonatal Intensive Care Unit, Department of Perinatal Medicine of University Children’s Hospital “A. Meyer” and the Division of Neonatology, Careggi University Hospital, in Florence.

There will be two investigative arms: CT-R and IM training. Both training programs will last 8-week.

All the infants will be clinically assessed at T0 (baseline, in the week preceding CT-R training/IM) and at T1 (i.e. in the week after the end of the 8-week programme of CT-R training/IM). T1 will be the primary endpoint. Then, all infants will be followed at T2 (i.e. 8 weeks after the end of intervention period) and at T3 (i.e. at 18 months of age). Figure 1 shows the detailed timeline.

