### Sample size

Based on the chosen primary outcome measure, Infant Motor Profile (IMP [31],), and on IMP results of a pilot study and of previously conducted RCT in preterm infants without congenital brain lesions [15, 19, 20] and considering a 80% power and a significant level of 0.05 and a effect size of at least 0.6, a sample of 38 children is required. However, considering also a 10% of drop-out rate, a minimum of 42 infants will be required. In order to facilitate parental work and participation in the project, eligible twins will be allocated into the same group.

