### Randomisation

Randomization will be done after enrolment: participants will be randomly assigned to CT-R training or IM group by the use of an automatic generation of 1:1 sets. A third party blind to clinical aspects of trial will manage these sets, sealing them in numbered envelopes.

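### The RCT is called paired, but neither randomisation nor analysis contains pairs, and the stated 38 infants do not give 80% power for the unadjusted unpaired comparison

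*Protocol article*

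**What the plan says.** The abstract (Methods/design) states: "This RCT will be multi-centre, paired and evaluator-blinded". The Study design section repeats that "a multicentre, evaluator-blinded, paired RCT will be carried out". No other section uses or explains the term.

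The sections that would have to carry out the pairing read as follows:

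- **Study sample and recruitment:** infants are assessed one by one against the eligibility criteria. No matching factor is named.
- **Randomisation:** after enrolment, participants are assigned "by the use of an automatic generation of 1:1 sets". A third party manages the sets in sealed, numbered envelopes. The size of a set is not given.
- **Sample size:** the inputs are "considering a 80% power and a significant level of 0.05" and "a effect size of at least 0.6", from which "a sample of 38 children is required"; then, "considering also a 10% of drop-out rate, a minimum of 42 infants will be required". The test, its sidedness and the type of effect size are not named. Eligible twins go to the same group.
- **Analyses:** the change from T0 to T1 is compared between CT-R and IM. The covariates are baseline motor level, lesion type and grade, family compliance and dose. There is no pair factor and no paired test.

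**The concern.** Calling an RCT paired asserts a design property: infants are matched, one of each pair goes to each arm, and the comparison is made within pairs. That implies balance on the matching factors and a gain in precision. Pairing has to be set up before allocation, so a later analysis plan cannot supply it.

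The label also affects how the sample size is read. The Sample size section does not say which test it is for, and a paired and an unpaired comparison need very different numbers at the same nominal effect size. If 38 belongs to a paired test while the trial is randomised and analysed unpaired, the stated 80% power does not apply to the primary comparison.

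**Working it through.** **Inputs** (Sample size section): power 80%, alpha 0.05, effect size 0.6, total 38, dropout 10%, final 42. Not stated: sidedness, whether 0.6 is a between-group standardised difference (d) or a mean paired difference divided by the SD of the paired differences (dz), and any correlation. Each reading was therefore tried.

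**Formulas** (noncentral t):

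- Paired, n pairs: df = n − 1, noncentrality = dz × √n. With 19 pairs: 0.6 × √19 = 2.615.
- Independent groups, n per arm: df = 2n − 2, noncentrality = d × √(n/2). With 19 per arm: 0.6 × √9.5 = 1.849.

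**Step 1: reproduce 38.**

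| Reading of the inputs | Infants needed for 80% | Power with 38 infants |
|---|---|---|
| Paired, one-sided | 19 pairs = 38 | 80.8% |
| Paired, two-sided | 24 pairs = 48 | 69.6% |
| Independent groups, one-sided | 36 per arm = 72 | 56.7% |
| Independent groups, two-sided | 45 per arm = 90 | 43.7% |

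The normal approximation gives 36, 44, 70 and 88 in the same order. Reading 0.6 as Cohen's f (d = 1.2) gives 12 per arm = 24. Of these, only the one-sided paired t-test returns exactly 38. The final figure then follows from 38 × 1.10 = 41.8, rounded up to 42.

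**Step 2: what the described trial gives.** For the unpaired, unadjusted two-sided comparison at d = 0.6, power is 43.7% with 19 per arm and 47.5% if all 42 infants (21 per arm) are retained. The effect detectable with 80% power at 19 per arm is about d = 0.93 two-sided, or 0.82 one-sided.

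**Step 3: could covariates make up the difference?** Under the normal approximation, n per arm = 2 × ((z for alpha + z for power)/d)² × (1 − r²), where r is the covariate-outcome correlation.

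- Two-sided: 2 × (2.802/0.6)² = 43.6, so 19 per arm needs r = √(1 − 19/43.6) = 0.75.
- One-sided: 2 × (2.486/0.6)² = 34.3, so r = √(1 − 19/34.3) = 0.67.

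The article gives no correlation. Over an assumed range, two-sided totals are 66 (r = 0.5), 56 (0.6), 46 (0.7) and 32 (0.8).

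**Step 4: if real pairs were formed.** Where 0.6 is a between-group d, dz = d/√(2(1 − ρ)), with ρ the within-pair correlation. Nineteen pairs then reach 80% only if ρ is about 0.49 one-sided or 0.61 two-sided. Neither is stated.

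**The case against.** The best defence is that *paired* is a loose word with no consequence. It may mean that each infant is measured at T0 and T1, or that the 1:1 sets are blocks of two, which are an allocation device and are often analysed unpaired. The article says neither, and neither would make the comparison between arms paired. The arithmetic for 19 pairs would equally fit a before-after test within one arm of 19 infants, but such a test does not size CT-R against IM.

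It is also fair to say that 38 need not come from pairing. The paired match requires a one-sided test, which is not stated, and a baseline-adjusted analysis with a high correlation reaches the same number. This stands: a reader may infer that the sponsor computed 38 from 19 pairs, but the document does not show it. What the document does show is that 38 is not supported for an unadjusted independent-groups comparison at 0.6.

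Three stronger inferences are not supported:

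- **Predictable allocation.** If sets held two infants, the second assignment would follow from the first. Set size is not given, however, and an article may leave it out. A third party holds the sealed envelopes.
- **Recruiters choosing who enters next.** The Blinding section says that clinical staff know infants' allocation. It does not say that enrolling staff follow the running sequence, and randomisation comes after enrolment.
- **Uncontrolled severity.** The Analyses section adjusts for baseline motor level and for lesion type and grade.

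**Conclusion.** The point holds as an internal contradiction with a consequence for power. The article states twice that the trial is paired, while its randomisation and analysis describe two independent groups. At the stated inputs, 38 infants give 80% power without covariate adjustment only under a one-sided paired t-test. For the comparison described, unadjusted power is 43.7% two-sided or 56.7% one-sided.

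These figures assume that 0.6 is a standardised mean difference on the analysed outcome, equal arms and a t-test. They ignore any precision gained from covariates, which could close the gap only at a correlation near 0.75 (0.67 one-sided). The true power of the adjusted analysis therefore cannot be stated from the document. The contradiction itself depends on none of these assumptions.

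**What to change.** Settle first whether pairs exist.

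- **If they do not:** delete *paired* from the abstract and from Study design. In Sample size, restate the power or detectable effect that 38 analysed (42 enrolled) infants give for the independent-groups analysis. Name the test, its sidedness, the definition of the effect size and any assumed baseline correlation with its source. Deleting the word alone is not enough, because 38 would remain unexplained.
- **If they do:** name the matching variables, randomise within pairs, include pair in the primary model, and restate power for that test with the assumed within-pair correlation. This is possible only before allocation starts.

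The first route costs wording and one recalculation, and the sponsor may have to report lower power or a larger detectable effect. Keeping 80% two-sided power at d = 0.6 without covariate gain would need 88 to 90 analysed infants, or 98 to 100 after 10% dropout (88/0.9 = 97.8; 90/0.9 = 100). The second route adds the work of matching and may delay allocation while a partner is found.

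Sets of varying, undisclosed size and a centre term in the model are optional, low-cost additions. The point does not depend on them.

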**Fig. 1 Fig1:**
[figure not shown]
Study design

This study will be structured in two parts: an observational phase and an intervention one.

The observational phase will be aimed to early detect the brain-lesioned infants at high risk for CP through standardization of traditional clinical procedures, based on the most updated existing criteria. The following intervention phase will be aimed at verifying and comparing, with a RCT, the efficacy of two EI models (CareToy-Revised and Infant Massage) in promoting neurodevelopment of high-risk infants.

### Observational phase

The observational phase will consist of a standardized follow-up for monitoring development of infants through ultrasound evidence of brain injury verified at the two Neonatology Units involved in this project. Monitoring will also include neurological assessment (HINE) and recording of spontaneous activity according to Prechtl (GMA) [25, 26].

These examinations will be performed at around term period and also 2–3 months after post-term age, in the Neonatology Unit designated for regular clinical follow-up examinations.

Moreover, as clinical recommended for high-risk infants, a brain MRI during spontaneous sleep will be performed within 6 weeks post-term. MRI protocol foreseen by this project includes structural images, already present in clinical protocols adopted by the involved clinics and necessary for definitive inclusion in the second intervention phase, and a brief period of functional MRI acquisition [27–29]. It will include two further series of images (GRE-EPI, TR / TE = 3000/50, FA = 90 °, FOV = 240 × 240 mm, matrix = 96 × 96, thickness = 3 mm), for a total duration of 4 minutes, according to a block diagram, with an alternation of visual stimulus presentation suitable for assessing visual system integrity that is used in movement perception (MT area of the parietal cortex). More specifically, the passive stimulus consists of image presentations, through appropriate non-magnetic glasses, for MRI that simulates coherent or incoherent movement.

### Intervention phase

In the interventional phase, infants will proceed with an early intervention, which could be CareToy-R or Infant Massage, according to allocation group. Each intervention will last 8 weeks, 5 days a week; during this experimental phase all infants will continue to receive standard care foreseen by National Health System. All other specific interventions (such as physical therapy or other treatments) will be recorded in a specific diary. Therapy protocols are described below.

### Study sample and recruitment

Participants will be recruited at Tuscany Neonatology Units in Pisa (Santa Chiara University Hospital) and in Florence (Meyer and Careggi Hospitals). The neonatological staff will assess eligibility of infants on the basis of inclusion and exclusion criteria prior to hospital discharge and staff will inform parents about study. If a family expresses interested in participating in the study, they will receive an introductory letter and an informative flyer. Recruitment must take place within the first year of age of the infant and, because of the characteristics of the interventional setting and exercises, before the complete acquisition of the trunk control in sitting position. If parents are willing to participate, they will be asked to sign a first agreement for admission to the observation phase and another one to partake in the intervention phase. As indicated above, Tuscan Region Paediatric Ethics Committee approved the clinical trial. Moreover, CT-R, as the previous CT, has been classified as a medical device without an EC mark, so an approval of a new clinical trial was requested and obtained by the Italian Ministry of Health.

Inclusion criteria will be the following:Abnormal or specific neurological signs at neurological examination of GMA or HINE, associated with one of the following conditionsPersistent brain ultrasound periventricular hyper-sonorityEvidence of cerebral haemorrhageEvidence of Periventricular Leukomalacia (PVL)Cerebral strokeModerate or severe asphyxia

Exclusion Criteria:Polymalformative syndrome or cerebral malformationsSevere retinopathy (III-IV degree)Severe sensory disturbances (deafness or blindness)

Moreover, to be enrolled in the intervention phase, additional inclusion criteria will be:Persistence of abnormal Spontaneous GMs evaluation according to Prechtl at 2–3 months post-term (absent or abnormal FMs)Persistence of abnormal/specific signs according to HINE

Finally, the inclusion criterion for the start of intervention phase (CareToy-R or Infant Massage) is based on motor requirements defined on the basis of Ages & Stages Questionnaire scores. In general, skills required to start EI range from initial head control to complete trunk control in sitting position. In other words, infants who have no initial head control or have acquired the sitting position cannot be admitted to the intervention phase. In the first case, it is necessary to wait until the infant can control the head within the first year of age, in the second case they will not allocated to the intervention phase.

To monitor motor progress, families will receive the section on “gross motor skills evaluation” of Ages & Stages Questionnaire (ASQ-3; gross motor [30]); as soon as the child reaches some pre-established motor skills (see below). Treatment can then start according to assignment group.score ≥ 10 from 3 to 4 monthsscore ≥ 5 < 50 from 5 to 6 monthsscore ≥ 10 < 30 from 7 to 8 months

The exclusion criterion is represented by a worsening of general clinical situation for intercurrent medical conditions or an onset of epileptic seizures.

